### Measures/Instruments

Recruitment rate: whether we will be able to recruit our target sample size of 200 participants (for the pilot study) in the time allotted in the project, which will be within 3 months. Retention rates will be measured in two ways: (a) within the intervention, whether participants would respond to queries about their smoking status; and (b) in the research, whether we could achieve follow-up rates high enough to conduct a larger randomized control trial (at least 75 %). Performance of the software that sends the program text messages (i.e., the messages needed to be sent successfully to all mobile phone carriers as designed).

### Quit messages

Types of Quit message show in Table 1 and Database of cessation messages show in Table 2.

**Table 1 Tab1:** Types of message for ‘happy quit’ program

Message type	Description	Examples
Invitation message	Describes the ‘happy quit’ program.	If you are an adult smoker intending to quit, please join our free SMS supported quit smoking activity. This program funded by CMB. This approach has been proven to be successful in some countries.
Preparing to quit	Describes steps and ways to take in preparing to quit smoking.	(1) Congratulations!! The hardest part—deciding to quit—is already behind you. Write down all of the reasons why you want to quit. (2) Before quitting, you should track your smoking; Try to cut down by 25 %, that is from 20 to 15 cigs per day. We’ll check in later. (3) Time for a Mini-Quit challenge. For the next 4 h, stay away from cigs. Practice dealing with cravings without smoking. We’ll check in 4 h.
Benefits of quitting	Describes the health-related, social and financial benefits of quitting.	(1) Figure out how much money you spend on cigarettes every year. What else can you do with that money? (2) For healthy and fresh breath, beautiful appearance, please keep on quitting! (3) There are so many benefits to being smokefree, such as looking well, having fresh breath, a good appetite and being full of energy. Tell your friends what you look forward to most! (4) Quitting smoking is the only way to stop damage to your body caused by smoking.
Seek for help	Describes seek for help to deal with crave, mood and reasons for quit.	Get more support whenever you need it by texting 7 (CRAVE), 8 (MOOD), 9 (why quit) at any time.
Coping and coping strategies	Describes and encourages the effectiveness and use of cognitive and behavioral strategies to avoid smoking during a craving or impulse to smoke.	(1) Treat every day like your quit day. Pretend like it is the first day without cigarettes and be prepared for temptation. (2) Don’t let things get you down. Your journey to smoke-free might be a struggle, but looking back will be amazing. Try to relax. Find an activity that is relaxing to you like listening to music, walking or taking a hot bath. (3) Think positively and find healthy outlets for stress or anger. If something bothers you, learn to relax quickly by taking deep breaths. Take 10 slow, deep breaths and hold the last one. Then breathe out slowly.
Discomfort and difficulties	Discusses discomfort associated with the quitting process and how the participant may see his or her discomfort as normal and how to cope with such discomfort	(1) Cravings become weaker every day that you don’t smoke. It’s harder in the beginning and will get easier with time. (2) Cravings last less than 5 min on average. Even the strongest cravings will go away after a few minutes. Focus on something else and remind yourself why you are smoke-free. (3) Drinking a lot of water will fight off cravings and help to keep you hydrated. (4) Try using sugarless gum, mints, toothpicks, straws or sunflower seeds to help keep your mouth busy.
Encouragement	Offers motivation and support to continue with quitting.	(1) 24 h smokefree! That is a MAJOR milestone! Be sure to reward yourself. Give, say or do something nice for yourself to celebrate your success. (2) 5 days smokefree! Smoking dulls taste buds. Luckily, your taste buds regenerate after several days without cigarettes. Treat yourself to a nice meal. (3) We know quitting is tough but stay strong! We all have bad days, and you will get through this. Do whatever to boost your mood-just don’t smoke.
Relapse	Describes how to prevent slips and the norms of slipping and how to get back on track; Clarifies reasons for quitting and to recommit; and teaches the participant to learn about what didn't work and new strategies	(1) You have come so far. Be careful when you go to a party, game or bar-do not let yourself slip. (2) You may not always feel as confident as you should and might slip. Keep trying no matter what. It Is possible to quit for your health. (3) How did you feel just before you smoked? Recommit to complete quitting—cutting down isn’t good enough for you! (4) Most smokers try to quit 6–7 times before they quit for good. Don’t quit quitting!

**Table 2 Tab2:** Database of cessation messages (will be modified during the pilot study)

Message type	Database of messages per quitting stage					
	Pre-quit	Quit day and day 2	Early quit	Late quit	Relapse	Encouragement to try quitting again later
Preparing to quit	170	0	0	0	0	0
Benefits of quitting	40	10	30	190	30	30
Coping and coping strategies	140	20	110	60	70	20
Discomfort and difficulties	10	30	30	10	20	0
Encouragement	30	10	50	30	50	30
Quitting skills	20	0	0	60	0	0
Relapse	0	0	0	0	50	0
Total (1350)	410	70	220	350	220	80

### Outcome measures

**Self-reported continuous smoking abstinence**: no more than five cigarettes smoked in the past week at 4 weeks follow-up and no more than five cigarettes smoked since the start of the abstinence period at 6 months of follow-up. **Point prevalence of abstinence**: not even a puff of smoke, for the last 7 days, at 4, 8, 12, 16, 20 and 24 weeks. Abstinence will be assessed by means of brief telephone interviews at each time point. **Cigarettes smoked per day:** number of cigarettes smoked per day within the past 4 weeks and the approximately total number of smoked cigarettes within the past 4 weeks.

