**Methods/Design:**

In this single-blind, randomized trial, undertaken in China, about 2000 smokers willing to make a quit attempt will be randomly allocated, using an independent telephone randomization system that includes a minimization algorithm balancing for sex (male, female), age (19–34 or >34 years), educational level (≤ or >12 years), and Fagerstrom score for nicotine addiction (≤5, >5), to ‘Happy Quit’, comprising motivational messages and behavioral-change support, or to a control group that receives text messages unrelated to quitting. Messages will be developed to be suitable for Chinese. A pilot study will be conducted before the intervention to modify the library of messages and interventions. The primary outcome will be self-reported continuous smoking abstinence. A secondary outcome will be point prevalence of abstinence. Abstinence will be assessed at six time points (4, 8, 12, 16, 20 and 24 weeks post-intervention). A third outcome will be reductions in number of cigarettes smoked per day.

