### Implications of our experiment

Tobacco use is a major cause of disease burden and the number one preventable cause of death in the world. About one-third of the world’s tobacco is produced and consumed in China. Among the general population of smokers, most report a desire to quit. Unfortunately, the availability of smoking cessation programs in China is extremely limited, and the majority of cessation attempts end in relapse. The rapid development of mobile health technology (mHealth) provides unprecedented opportunities to improve health services and to reach underserved populations, and the effectiveness of text message mobile phone programs to improve smoking cessation has been reported in other countries.

Considering the extreme shortage of smoking cessation programs in China, and the efficacy of mobile phone text message-based program for smoking cessation reported in other countries, we propose to design such a population-based widely accessible smoking cessation program in China. This proposed study is designed to determine the effectiveness of mobile phone-based text message interventions (‘Happy Quit’) for smoking cessation in China, which will be assessed by self-reported smoking abstinence at 4, 8, 12, 16, 20 and 24 weeks post-intervention. This proposed study has important implications in providing valuable insights into bridging the gap between need and services received for smoking cessation interventions and tobacco use prevention in China. It will also serve as a mHealth model for extending the public health significance of interventions, such as mental health interventions.

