### Procedures

We will advertise this service to smokers on the radio, bus billboards and online (e.g., websites, QQ, WeChat) and in newspapers, hospitals and pharmacies. Potential participants will register their interest by sending a text message. Research assistants then will telephone respondents to assess eligibility and collect baseline data.

In this single-blind, randomized trial, undertaken in China, smokers willing to make a quit attempt will be randomly allocated, using an independent telephone randomization system that includes a minimization algorithm balancing for sex (male, female), age (19–34 years, >34 years), educational level (to age ≤12 years, >12 years), and Fagerstrom score for nicotine addiction (≤5, >5), to a mobile phone text messaging smoking cessation program (‘Happy Quit’), comprising motivational messages and behavioral-change support, or to a control group that receives text messages unrelated to quitting. The system will automatically generate intervention or control group texts according to the allocation. Outcome assessors will be masked to treatment allocation.

Participants will be allocated to either a control group or to a group that receives the mobile-based smoking cessation program. All participants will be free to participate in any other smoking cessation service or support that they wish to use if possible and available. All Participants in both the intervention group and control group will be asked to set a quit date within one month of randomization.

Messages will be developed with the input of smokers and smoking cessation professionals. The intervention will include motivational messages and behavior-change techniques. Messages will encourage participants to persevere with the quit attempt and will focus on their success so far. The motivational messages will provide positive feedback and emphasize the benefits achieved by quitting and provide information about the consequences of smoking, how to quit and stay quit, and how others would approve of successful abstinence. The behavior change messages will prompt participants to get rid of cigarettes, ashtrays, and lighters and to avoid environments where they would normally smoke, and encourage participants to identify the challenges of quitting and plan how to overcome them. The messages also promote the use of nicotine replacement therapy if possible and available.

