Participants who allocate to the intervention group will receive this program of interventions, which will be based around setting a quit date within 30 days of randomization. As described above, they will receive regular, personalized text messages providing smoking cessation advice, support and distraction. This content will also cover information relevant to quitting—for example, symptoms to expect on quitting, tips to cope with craving, tips to avoid weight gain and improve nutrition; advice on avoiding smoking triggers; instructions on breathing exercises to perform instead of smoking; motivational support (for example feedback on amount of money and life years saved) and distraction (for example, general interest, sports, fashion, trivia, travel). The messages will be developed by a multidisciplinary team including young adults, health related researchers and experts in cognitive behavioral therapy, and smoking cessation. An algorithm based on keyword matching will be developed to match participant characteristics (preferences, smoking history, barriers to cessation, etc.) with a database of over 1000 text messages so that an individualized program will be provided.

A quit day will be negotiated with each participant, and five messages will be sent per day for the time leading up to the quit day and the following 12 weeks. On the quit day, a free month of outgoing text messaging also begins, with participants encouraged to tell all their friends and family they are quitting on that day. This process will encourage communication and support, and also help with distraction, given the time that will spend in writing and receiving text messages. Several other text message based services will also be provided for the intervention group: Quit buddy (participants with similar characteristics and quit days will be put in touch with each other); text crave (participants could ‘pull’ text messages on demand by sending a text message to a short code number and they would receive a tip on how to get through their cravings); and TXT quizzes (questions will be sent out, following by answers the next day).

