Twelve weeks after randomization, coinciding approximately with the end of the free text messaging month, the intervention will become much less intensive, with the number of sent text messages reduced from five per day to three per week until the end of the 24 week (that is, six month) follow up. These messages will focus on maintaining cessation among those who had quit. Control group participants only will receive one text message every week, thanking them for being in the study, providing study centre contact details, and reminding them of the time until their free month at the end of follow up.

Anyone who completes follow up (a total of 24 weeks) will be rewarded with a free month of text messaging and 100 CNY mobile phone based payment (whether they quit or not), a reminder of these benefits will be sent to the participants at the beginning of the study and each month. All participants will be checked at 4, 8, 12, 16, 20, 24 week points about continuous smoking abstinence, point prevalence of abstinence, how many cigarettes per day during the last 4 weeks and past 1 week if they are still smoking, levels of craving, weight and so on. Symptoms of anxiety and depression, sleeping quality will be only asked at before quit day, 8 week, and 24 week points, and a phone call will be made for their significant other (e.g., family member, friend) to make a further confirmation about their quit status.

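### The primary endpoint has no single time origin, and counted from randomisation its 4-week condition fails participants who quit on an allowed late date

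*Protocol article*

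**What the plan says.** Outcome measures defines continuous abstinence in two parts. The first is "no more than five cigarettes smoked in the past week at 4 weeks follow-up"; the second is "no more than five cigarettes smoked since the start of the abstinence period at 6 months of follow-up". Neither the origin of the 4 weeks nor the start of the abstinence period is given.

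Other sections supply origins, but not the same one:

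- **After the intervention.** The Abstract (Methods/Design) says "Abstinence will be assessed at six time points (4, 8, 12, 16, 20 and 24 weeks post-intervention", and the Background (Implications of our experiment) repeats it: "assessed by self-reported smoking abstinence at 4, 8, 12, 16, 20 and 24 weeks post-intervention".
- **Randomisation.** Procedures steps the messages down 12 weeks after randomisation, "reduced from five per day to three per week until the end of the 24 week (that is, six month) follow up". It gives 24 weeks as the total length of follow-up.
- **Quit day.** Procedures also counts the 12-week intensive phase from the quit day, and places one measurement of anxiety, depression and sleep before the quit day.

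The quit date itself is flexible: "All Participants in both the intervention group and control group will be asked to set a quit date within one month of randomization". The description of the intervention arm gives the window in days: "which will be based around setting a quit date within 30 days of randomization".

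**The concern.** A 7-day look-back at week 4 makes sense only if everyone's permitted quit date comes before it. If week 4 is counted from randomisation, it ends on day 28, while the quit date may be as late as day 30. Some participants who do exactly what the plan asks are then still expected to be smoking during the look-back. They are scored as failures on the primary outcome whatever they do later.

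This lowers the event rate in both arms and costs power. It could also distort the comparison if quit dates fall differently in the two arms. The window is common to both, but the intervention programme is built around a negotiated quit day with preparatory messages, whereas controls get one message a week.

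**Working it through.** **1. Can the assessments be timed after the intervention?** Messages run to the end of week 24. Read literally, contacts 4 to 24 weeks later would fall at weeks 24 + 4 = 28 to 24 + 24 = 48. Procedures gives 24 weeks as the total follow-up, so this origin is excluded by the article itself.

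**2. Are the two remaining origins equivalent?** No. With quit day q between 0 and 30 after randomisation, the intensive phase ends on day 84 if counted from randomisation, and on day 84 + q (84 to 114) if counted from the quit day. At a week-24 contact counted from randomisation (day 168), the abstinence period is 168 − q days, so 138 to 168 days.

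**3. Who fails at week 4 on the randomisation clock?** Day 0 is randomisation, the contact is on day 28, and the look-back is days 21 to 27. Take a participant who smokes c cigarettes a day until quit day q and none afterwards. Smoking days in the look-back = min(7, max(0, q − 21)). The criterion fails when c × (that number) > 5. The article requires only daily smoking, so c may be as low as 1.

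| c per day | Smoking days needed to exceed 5 | Failing quit days | Share of days 1–30 |
|---|---|---|---|
| 6 or more | 1 | 22–30 | 9/30 = 30% |
| 2 | 3 | 24–30 | 7/30 = 23% |
| 1 | 6 | 27–30 | 4/30 = 13% |

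Quit days 29 and 30 have not yet arrived at the contact. The shares assume quit dates spread evenly over days 1 to 30; the article gives no distribution.

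**4. On the quit-day clock.** The look-back is days 21 to 27 after quitting, so it lies wholly after q for every q. Nobody fails by construction. The last contact falls on day 168 + q, that is 168 to 198 after randomisation.

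**5. Effect on power.** Statistical methods gives a control rate of about 5%, 1000 per group and two-sided alpha 0.05, but no intervention rate. I therefore assume two: 8% and 10%. The 10% value is plausible because 5% vs 10% at 80% power needs 435 per arm, and 435/0.9 = 484, close to the article's 486. Other pairs fit that figure as well.

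Power = Φ{[(p2 − p1)√n − 1.96√(2p̄(1 − p̄))] / √(p1(1 − p1) + p2(1 − p2))}, with n = 1000 and p̄ the mean of the two rates. Losing 30% of successes in both arms multiplies each rate by 0.7; this assumes that success does not depend on the quit date.

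- 5% vs 8%: (0.9487 − 1.96 × 0.3486)/0.3480 = 0.763, power 0.777.
- 3.5% vs 5.6%: (0.6641 − 1.96 × 0.2947)/0.2943 = 0.294, power 0.615.
- 5% vs 10%: (1.5811 − 1.96 × 0.3725)/0.3708 = 2.295, power 0.989.
- 3.5% vs 7%: (1.1068 − 1.96 × 0.3154)/0.3144 = 1.554, power 0.940.

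**The case against.** The strongest reply is that the endpoint works if the weeks are counted from the quit day, and that nothing in Outcome measures says otherwise. That is correct. A reader might infer that the endpoint is unworkable; the article does not support this, because the failures arise on one of two readings, and there only for roughly the last 4 to 9 days of the quit window. But the article never adopts the quit-day clock for its assessments, and the step-down after 12 weeks from randomisation within a 24-week follow-up points the other way.

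Second, timing the assessments after the intervention looks like a slip, since the 24-week total shows that it cannot be meant. This also stands: no reader should conclude that follow-up runs to week 48. Yet it is the only origin the article states for the assessments, so removing it leaves none.

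Third, a condensed article may leave the operational start of abstinence to a fuller document, and the quit date is its natural start. Silence on that alone would not be a finding. The conflict between the article's own sections is.

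Fourth, a reader might infer that the arms will be biased against each other. The quit window is the same in both, and the article gives no sign that quit dates will differ or by how much. Bias is possible, but its size is unknown and no figure for it can be defended.

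**Conclusion.** The point holds as a contradiction in the timing of the primary outcome. The article uses three origins, one of them impossible, and the remaining two can score the same participant differently.

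If randomisation is the origin, quit dates in the last 4 to 9 days of the 30-day window fail the 4-week condition despite full later abstinence. That is about 13% to 30% of participants if quit dates are evenly spread. This misclassification does not depend on the treatment effect. The cost in power does: at 30% loss it is 16 percentage points for an assumed 5% vs 8% (0.777 to 0.615) and 5 points for an assumed 5% vs 10% (0.989 to 0.940). Fewer failing quit dates would cost less. If the quit day is the origin, there is no loss at all.

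It needs settling before any outcome is scored, because the choice decides who is a success.

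**What to change.** Reconcile the Abstract, Background (Implications of our experiment), Procedures and Outcome measures. Delete *post-intervention* as a time label. State one origin for all outcome assessments and one start of the abstinence period, identical in both arms, such that the 4-week look-back cannot precede an allowed quit date.

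The simplest way that keeps the existing endpoint is to record each participant's quit date at the baseline call, before allocation, and to count the 4-week to 24-week assessments from that date. Recording it before allocation also prevents the assigned arm from influencing the date used for scoring. The cost is a change of wording and contact dates that shift with the quit date, the last by up to 30 days after the present day 168.

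If the randomisation clock is kept, the 4-week condition should leave the primary definition and be reported separately; the interviews themselves need not change. Replacing the whole primary endpoint is more than this problem requires.

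The two statements of when the intensive message phase ends also need to be reconciled. Which schedule is right is for the investigators to decide.

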### Independent variables

Characteristics of cigarette smokers: age, gender, marital status, education years, smoking duration, severity of nicotine dependence, weight, sleep quality, levels of anxiety and depression et al. These will be collected by phone call and using a series of questionnaires, such as questionnaire of demographic characteristics, Pittsburgh sleep quality index, state-trait anxiety inventory, Beck depression rating scale, Fagerstrom Test for Nicotine Dependence.

### Statistical methods

**Power estimation:** On the basis of the results of the recent review paper [20] and the large sample size study published in the Journal of Lancet [15], we estimated that the control group quit rate would be around 5 % (ranged from 4.9 to 27.6 %) and loss to follow-up will be 10 %, with 95 % as an accepted standard for statistical significance. According to a power analysis, only 486 participants will be required in this group. However, given that none of the study from China, we plan to assess 4000 participants, and 2000 participants (1000 participants in each group) will be eligible and randomize to intervention or control groups. With 10 % loss to follow-up, we will have a 90 % of participants available for analyses, which will provide sufficient power to detect a difference.

**Comparison between Intervention group and control group:** For the data, *t* test, Chi-square test and logistic regression will be used for the comparison of the self-reported continuous smoking abstinence, point prevalence of abstinence, cigarettes smoked per day between the two groups. Repeated measures analyses of variance will be used for the comparison of levels of craving, weight, sleep quality, levels of anxiety and depression between the two groups. An alpha level of 0.05 (two-tailed) will be chosen for all statistical tests in this study. For the primary analysis we will use multiple imputation, which uses the observed predictors of outcome and the predictors of loss to follow-up to impute missing outcome data, thus attempting to correct for any potential bias caused by it (using the intent-to-treat principle, missing will be counted as smoker).

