## Research design and methods

### Hypotheses and theoretical model

Primary Hypothesis: We hypothesize that ‘Happy Quit’ will be tested as an effective, feasible and affordable smoking cessation program in China. To be specific, the text messages intervention group will have higher rates of self-reported continuous smoking abstinence and point prevalence of abstinence when compared to control-group; and by assessing the number of cigarettes smoked per day, the text-based intervention will help those relapse smokers smoke fewer cigarettes than before. Secondary Hypothesis: Mobile phone-based text message interventions (‘Happy Quit’ program) for smoking cessation will have wider influence on smoking cessation in China.

Theoretical model: Fig. 1 illustrates the theoretical model. In this model, text messaging could be applied in healthcare widely: settings range from primary care to community care services to public health; purposes from behavior modification to disease management, treatment and medication adherence to data collection; populations vary from children and adolescents to elderly, from cigarette smokers to Patients with mental illness and other diseases. Figure 2 Shows the worksheet for short message service (SMS) implementation planning for ‘Happy Quit’ program.

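### Cigarettes per day is described as a reduction but defined as a level; the only listed test that fits it is a t test with no stated baseline covariate, and lost participants and quitters have no stated count

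*Protocol article*

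**What the plan says.** Four sections of the protocol article describe this outcome, and they differ.

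- Abstract, Methods/Design: "A third outcome will be reductions in number of cigarettes smoked per day".
- Hypotheses and theoretical model, within the primary hypothesis: "the text-based intervention will help those relapse smokers smoke fewer cigarettes than before".
- Outcome measures: "number of cigarettes smoked per day within the past 4 weeks and the approximately total number of smoked cigarettes within the past 4 weeks". This is a follow-up level, with no baseline and no difference in it.
- Procedures: at each check the count is asked of participants who continue to smoke. No value is stated for those who have stopped.

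Statistical methods names three tests jointly (t test, chi-square, logistic regression) for continuous abstinence, "point prevalence of abstinence, cigarettes smoked per day between the two groups". It does not assign a test to each outcome. Repeated measures analysis of variance is kept for other outcomes: "Repeated measures analyses of variance will be used for the comparison of levels of craving, weight, sleep quality, levels of anxiety and depression".

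On missing data, the same section ties multiple imputation to the primary analysis and adds "using the intent-to-treat principle, missing will be counted as smoker". On baseline, Procedures says: "Research assistants then will telephone respondents to assess eligibility and collect baseline data". It does not list a cigarette count among those data, but a reduction cannot be computed without one.

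**The concern.** A level and a reduction are different variables. So are a mean over everyone randomised and a mean over people who still smoke. The article does not settle which is meant, although the outcome sits inside the primary hypothesis.

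The named test is also weaker than one available from the same data. A t test on the level makes no use of how much each person smoked at entry. A t test on the change uses it, but with a fixed coefficient of one, which adds noise unless the correlation is high. Entering the baseline count as a covariate avoids both losses.

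Finally, smoker is a status and not a number of cigarettes, so the stated scoring rule cannot fill in a missing count. If people without a count drop out, the comparison depends on loss being alike in the two arms. If quitters drop out as well, it compares subgroups formed after randomisation.

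**Working it through.** The article gives no standard deviation, effect size, power or sample size for cigarettes per day, so there is no figure of its own to reproduce. Its 486 comes from the quit-rate power analysis and has no bearing here.

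**Inputs from Statistical methods:** 1000 per arm, 10% loss (so 900 per arm observed, and 2000 × 0.10 = 200 people without a count), two-sided alpha 0.05, control quit rate about 5%.

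**Assumed, because not given:** baseline/follow-up correlation r of 0.3, 0.5 or 0.7; equal standard deviations at the two times; 12 cigarettes per day among smokers; 5% or 10% abstinent in each arm with no treatment effect; all lost people are smokers.

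**Step 1, precision.** Variance of the arm difference, with a t test on the level set to 1:

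- change score: 2(1 − r)
- baseline-adjusted: 1 − r²

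| r | level | change | adjusted | SE, adjusted/level | SE, adjusted/change |
|---|---|---|---|---|---|
| 0.3 | 1 | 1.40 | 0.91 | 0.954 | 0.806 |
| 0.5 | 1 | 1.00 | 0.75 | 0.866 | 0.866 |
| 0.7 | 1 | 0.60 | 0.51 | 0.714 | 0.922 |

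The ordering does not need equal standard deviations. With baseline SD s0 and follow-up SD s1, the change variance minus the adjusted variance is s0² + s1² − 2r·s0·s1 − s1²(1 − r²) = (s0 − r·s1)², which is never negative. The level variance minus the adjusted variance is r²·s1², also never negative.

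At 900 per arm, the difference detectable with 90% power is (1.960 + 1.282) × √(2/900) = 0.153 SD for the level. With adjustment it is 0.146, 0.132 and 0.109 SD at r = 0.3, 0.5 and 0.7.

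**Step 2, leaving out the lost.** Let p be the proportion abstinent and L the loss in an arm. The observed mean is 12 × (1 − p − L)/(1 − L).

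- Equal loss of 10%, p = 0.10: 12 × 0.80/0.90 = 10.67 in both arms, difference 0.
- Loss 15% (intervention) against 5% (control), p = 0.05: 12 × 0.80/0.85 = 11.29 against 12 × 0.90/0.95 = 11.37, difference −0.07.
- The same loss, p = 0.10: 12 × 0.75/0.85 = 10.59 against 12 × 0.85/0.95 = 10.74, difference −0.15.

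The true difference is 0 in each case, so −0.07 to −0.15 cigarettes per day is bias. It favours whichever arm loses more people. With an assumed SD of 8, the SE is 8 × √(1/850 + 1/950) = 0.38, and a 5% test rejects about 5.4% and 6.8% of the time respectively.

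**The case against.** The strongest reply is that the article states nothing invalid. A two-sample t test is sound under randomisation. Covariates and missing-data rules for a third outcome are often left to an analysis plan, which is not shown here. The gain from adjustment depends on a correlation the article does not give. All of this stands, and it limits the point to avoidable imprecision and an unsettled definition.

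Four stronger readings are tempting, and the text does not carry them.

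- *The t test ignores baseline.* A reader might infer this from the absence of a covariate. A t test on the reduction would use the baseline count, only less efficiently than a covariate would.
- *The result describes responders only.* This is an inference from imputation being tied to the primary analysis. Nothing in the article bars imputing the count.
- *Large false-positive inflation.* With 30% against 10% loss and 10% abstinent, the formula above gives 12 × 0.60/0.70 = 10.29 against 12 × 0.80/0.90 = 10.67, a difference of −0.38, and about 16% rejection at SD 8. The article plans 10% loss and about 5% quitting in the control group. With 5% abstinent, even that extreme loss gives −0.19 and 7.6%.
- *The sleep and mood test dilutes the effect by averaging in the pre-quit value.* The article does not say which term of the repeated measures analysis is tested. It also fixes the first value only loosely: "sleeping quality will be only asked at before quit day, 8 week, and 24 week points". The quit day may fall up to a month after randomisation, with messages already being sent, so that value is not certain to precede allocation.

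What the reply does not remove is the conflict between a reduction and a level, the unstated value for quitters and the lost, and a named test that a free alternative matches or beats on either reading.

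**Conclusion.** The point holds as a matter of precision and definition, not of validity. Relative to a t test on the level, baseline adjustment cuts the variance by 9%, 25% and 49% at assumed correlations of 0.3, 0.5 and 0.7. Relative to a t test on the change, it cuts it by 35%, 25% and 15%, since (1 − r²)/(2(1 − r)) = (1 + r)/2. The percentages assume equal standard deviations at the two times; the ordering does not.

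Bias from missing counts is conditional on lost people being left out. It is nil with equal loss and about 0.07 to 0.15 cigarettes per day at 15% against 5% loss, under the assumed abstinence and smoking rates. The article should be changed here because the outcome belongs to its primary hypothesis and the remedy costs almost nothing.

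**What to change.** In Statistical methods, with matching wording in the abstract and Outcome measures:

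1. Define cigarettes per day once, for all randomised participants, with abstinent people entered as 0. State which abstinence definition gives the zero, because continuous abstinence as defined tolerates up to five cigarettes.
2. Compare the arms with a linear model containing arm and the baseline cigarettes-per-day count, with robust standard errors, and report the adjusted mean difference.
3. Include the count in the multiple imputation already planned. As a sensitivity analysis, give lost participants their baseline count.
4. Secondary: for weight, sleep, anxiety and depression, use the follow-up values as outcomes and the baseline value as a covariate, provided that value is taken before allocation.

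The cost is wording only, with no added participants or visits. It assumes that the baseline telephone call records the cigarette count, which a reduction already requires. Item 4 also needs confirmation that those measures are collected before allocation.
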